## Background

Non cephalic presentation (NCP) in childbirth involves various risks to both the mother and the foetus. NCP includes breech, oblique and transverse presentations. The incidence of breech presentation (BP) is 20% at 28 weeks' gestation, although spontaneous version tends to occur more frequently [1], such that in only 3–4% of women with a full-term pregnancy is the foetus BP [2]; in Spain, NCP represents 3.8% of all births [3].

Until week 28–32, and under normal conditions, the foetus has a high degree of mobility, and remains in an unstable situation. From the latter date, the foetus adapts itself to the shape of the uterus, adopting a head-down posture, and normally remains so until birth. There are various reasons that may prevent the foetus from moving into the cephalic position, the most common of which, according to a specialized study [4] are: a) pre-term birth; this factor is more influential with lower gestational ages (35% before week 28, 16.8% from week 28–31, 8.9% from week 32–36 and 3.7% from week 36–41); b) foetal malformations (those most commonly related to NCP are anencephaly, hydrocephaly, spina bifida, polycystic kidneys and Potter's Syndrome, as well as trisomies 13, 18 and 21; c) multiple pregnancy, in which the incidence of NCP is 7 times greater than in the case of a singleton pregnancy. High levels of perinatal mortality and morbidity are known to be associated with NCP, due mainly to prematurity, congenital malformations, hypoxia or birth trauma [5,6], and so a breech delivery is a birth that is categorized between dystocia and eutocia.

The most common technique used to end gestation in cases of NCP is that of caesarian section. From the results of the study by Hannah et al. [7], in October 2000, from the results produced by the Term Breech Trial Collaborative Group, and from the Cochrane Collaboration review [8], we now know that foetuses which are extracted by elective caesarian section have a lower level of perinatal morbi-mortality than those delivered vaginally. However, this technique does not prevent traumatic lesions to the foetal head and neck and, moreover, it is associated with an increase in maternal morbidity [8-11]. In addition to the increase in morbidity immediately following a caesarean section, there may occur other types of complications, such as intraabdominal adhesions, with the possibility of later infertility and risks in future pregnancies caused by the uterine scar [11].

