Acupuncture and moxibustion are therapeutic techniques found in traditional Chinese medicine. They have been employed since ancient times, and specific recommendations in Chinese texts include the application of heat (moxibustion) by the combustion of *Artemisia vulgaris *(moxa) over an acupuncture point in order to correct NCP [12,13]. This latter point, known as *Zhiyin *(BL67) is located in the outer corner of the little toenail. In addition to moxibustion, acupuncture may also be used, either alone or in association with moxibustion, on this or other points, although it has been found that the highest level of effectiveness is associated with the application of moxibustion alone [14]. A Cochrane review [15] concluded that there is insufficient evidence from the studies included in its analysis, and observed that there have been few well-designed studies (only 3 are included in the review) and that most of them used a small sample. Some studies with a larger sample, such as that by Kanakura et al. [16], were not randomized. A larger, systematic review that we have carried out this year (manuscript submitted for publication), with the inclusion of new studies performed to date, and with the incorporation of those published in Chinese in the last 10 years, shows that studies contain to be of low methodological quality. We estimate a correction rate of 70% (versus 50% in control groups) among pregnant women treated with moxibustion. Among the studies carried out so far, no reports have been made of side effects, although the smoke generated while the moxa is burned may irritate the respiratory tracts. Nevertheless, there is no evidence to support this hypothesis [15]. Neri et al. [14,17] have made a cardiotocographic study of the effects of moxibustion on foetal heartbeat, and concluded that no harm is caused by this process.

The present study is funded by the Health Ministry of the Andalusian Regional Government (Project No. 0053/2007).

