### Subjects

Pregnant women recruited by their obstetrician during the third scheduled echography (at week 32 of gestation), after confirmation of NCP. These pregnant women will be referred to midwives at the participating Primary Healthcare Clinics belonging to the Andalusian Public Health System in the provinces of Sevilla, Huelva, Cádiz and Málaga. The pregnant women will be informed as follows: "If you decide to take part in the study, in addition to being given various postural recommendations, you will be included, at random, in one of the three treatment groups. In two of these, moxibustion techniques will be applied at a specific point on each foot, while in the third group the standard treatment procedures followed in the healthcare system will be applied, to see if spontaneous correction occurs. If you are assigned to one of the two groups in which moxibustion is applied, then, according to the random choice made, you may be given moxibustion at a point that has been proved to be effective, or on the contrary, at a point that has not proved to be of any value for the aims of our study". The pregnant women will also be informed of the possible risks associated with the use of moxibustion (respiratory discomfort from the smoke inhaled, the possibility of burns or of ulceration of the skin) and that they may conclude their participation in the study at any time, with no type of penalty or loss of benefits they would otherwise be entitled to.

The subjects included in the study will be pregnant women, aged at least 18 years, whose foetus is in a non cephalic position (diagnosed by physical examination and by echography), with a gestational age of 33–35 weeks (estimated by echography), normal foetal biometry, who have signed their informed consent and who have not previously received moxibustion treatment to correct the position of their unborn baby. Criteria for exclusion will include twin pregnancy, pelvic defect, previous uterine surgery, foetal malformation or chromosome disorder, uterine malformation, risk of premature birth (preterm uterine contractions and/or initial dilation or shortening of the cervix with a Bishop's score of 4), uterine fibromas > 4 cm, treatment with tocolytic drugs, heart or kidney disease affecting the mother, other pregnancy-related complications, or incapacity to complete the questionnaire or respond to the assessor's questions.

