### Sample size

The sample size has been predetermined at n = 492 patients, for a significance level of 95%, a power of 90% and a difference in the success rates of either of the intervention groups (A or B) with the control group (C) of 20%, assuming a dropout rate of 25%. These values were calculated using SamplePower version 2 software.

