### Outcome measures

#### Primary outcome

The rate of cephalic presentation at term will be taken as the primary endpoint variable.

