#### Secondary outcomes

Secondary outcomes will include the rate of cephalic presentation at week 38 of gestation (CP38) (determined by echography) and the number of days of treatment received until version occurs. The intervention allocation to the moxibustion groups (true or sham) will be controlled by asking the subject: "What type of treatment do you think you received?" Three possible answers may be given: A) Real; B) Sham; C) I don't know. The following sociodemographic covariables will be recorded: age, race, educational level, occupation, level of income, occupational activity, weight (kg), height (cm). In addition, these obstetric-gynaecological variables will be recorded: gestational age when subject was included in the study, determined by foetal biometry; type of presentation, determined by echography (characterized as breech, oblique or transverse presentation); foetal biometry (biparietal diameter, abdominal diameter and length of femur) [week of gestation when biometry is performed]; location of the placenta (categorized as anterolateral or posterior), parity (number of previous births), and previous miscarriages. The following security variables (in the first session) will be used: maternal heartbeat prior to the stimulus; foetal heartbeat prior to the stimulus; maternal heartbeat at 5 minutes after the stimulus; foetal heartbeat at 5 minutes after the stimulus. The security variables determined during the treatment will be recorded on the self-reported questionnaire which is completed by the subjects after each home treatment session, with data on foetal movements, uterine contractions, maternal heartbeat and any other incident following the stimulation. Finally, a number of other variables related to the birth will be recorded, including gestational age at birth, weight of the neonate, sex of the neonate, type of birth (vaginal or caesarean section), and APGAR score at 1 and 5 minutes (Figure 2).

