For the primary outcome variable, logistic regression models will be created, using ITT analysis. These will include, firstly, the group variables (experimental vs control), taking the control group (usual care) as the reference level. Then, the model will be adjusted for the variables of age, parity and weeks of gestation at randomization (the baseline variables). Adjustment will also be made for other possible confounders (the variables that are imbalanced in the baseline analysis) using criteria of statistical significance (*P *< 0.05) and of confusion (change of over 10% according to the magnitude estimator – the incidence odds ratio). The detection of possible interactions with the "treatment group" variable will be carried out by means of statistical significance criteria for the corresponding terms of interaction, introducing the relevant additive and multiplicative interaction variables. The level of significance will be set at <0.05 α for the global comparisons, although this level will be penalized by the existence of an intermediate level, as explained below. A cost effectiveness analysis, from the standpoint of the Andalusian Public Healthcare System, will be performed.

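### Baseline type of presentation is recorded but left out of the fixed covariates of the primary model, and can enter only through a data-driven imbalance rule

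*Protocol article*

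**What the plan says.** All references are to the protocol article.

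- **Entry.** The Background defines the population broadly: "NCP includes breech, oblique and transverse presentations". The Subjects section admits any woman "whose foetus is in a non cephalic position (diagnosed by physical examination and by echography"), with no restriction to breech.
- **Outcome.** "The rate of cephalic presentation at term will be taken as the primary endpoint variable".
- **Baseline record.** Under Secondary outcomes, the obstetric variables to be collected include "type of presentation, determined by echography (characterized as breech, oblique or transverse presentation").
- **Randomisation.** Allocation is 1:1:1 in blocks of 12, stratified by clinic. Type of presentation is not a stratification factor.
- **Primary model.** The Statistical analysis section puts group in first. "Then, the model will be adjusted for the variables of age, parity and weeks of gestation at randomization (the baseline variables"). Other variables are adjusted for if they are imbalanced in the baseline analysis, using P < 0.05 and a change of over 10% in the odds ratio as criteria. An earlier paragraph of the same section says imbalance will be assessed through ratios of means and proportions. Interactions with treatment group will be screened by significance, but no candidate variables are named.
- **Expected rates.** From the authors' own review: "We estimate a correction rate of 70% (versus 50% in control groups) among pregnant women treated with moxibustion".

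**The concern.** Type of presentation is the starting value of the quantity that the primary outcome measures at the end. Such a variable is usually a leading candidate for a fixed covariate, and here it is collected anyway. The plan names a fixed list that omits it and leaves it to a rule triggered by observed imbalance.

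Two things are at stake. The first is precision: if the types differ in how often they turn spontaneously, a model without type wastes some of the information collected. The second is pre-specification: whether type is in the model becomes known only after the data are seen. With valid randomisation, a baseline imbalance is a chance event and says nothing about whether a variable predicts outcome, so the rule selects on the wrong property.

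This is not a detail left to a fuller document. The article states both the covariate list and the admission rule, and the point concerns what they say.

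**Working it through.** **1. The plan's own sample size.** The Sample size section gives "for a significance level of 95%, a power of 90" per cent, "a difference in the success rates of either of the intervention groups (A or B) with the control group (C) of 20" percentage points, and 25% dropout. It states no control rate, so 50% against 70% is taken from the Background. Two-sided 0.05, pooled formula, no continuity correction:

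n = [1.96·√(2·0.6·0.4) + 1.2816·√(0.5·0.5 + 0.7·0.3)]² / 0.2² = (1.358 + 0.869)² / 0.04 ≈ 124 per arm.

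124 / 0.75 gives 166 per arm, and 3 × 166 = 498, within about 1% of 492. Conversely, 492 × 0.75 / 3 = 123 evaluable per arm, with power 89.8%. The stated size reproduces, and adding a covariate does not change it. At the two-sided 0.025 set in the Intermediate analysis section, power at 123 per arm is 83.7%.

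**2. What has to be assumed.** The documents give neither the share q of oblique or transverse lies at entry nor version rates by type. Assume q = 10-30% and a control version rate p₁ = 65-85% for those lies. Set the breech rate so that control stays at 50% overall: p₀ = (0.5 − q·p₁)/(1 − q).

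**3. Simulated power.** 4,000 trials per scenario, 123 per arm, Wald test of arm in logistic regression at two-sided 0.025, marginal rates fixed at 50% and 70%. Variance explained in the control arm = q(1 − q)(p₁ − p₀)²/0.25.

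| q | p₁ | p₀ | Variance explained | Power unadjusted | Power adjusted | Gain (points) |
|---|---|---|---|---|---|---|
| 10% | 80% | 46.7% | 4.0% | 83.2% | 84.7% | 1.5 |
| 20% | 65% | 46.3% | 2.3% | 84.0% | 85.0% | 1.0 |
| 20% | 80% | 42.5% | 9.0% | 83.3% | 85.8% | 2.5 |
| 20% | 85% | 41.3% | 12.3% | 83.2% | 87.7% | 4.5 |
| 30% | 70% | 41.4% | 6.9% | 84.1% | 86.4% | 2.3 |
| 30% | 80% | 37.1% | 15.4% | 82.9% | 87.7% | 4.8 |
| 20% | 50% | 50% | 0% | 83.4% | 83.7% | 0.3 |

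The simulation error of one power figure is √(0.84·0.16/4000) ≈ 0.6 points. A second simulation of five of the six prognostic scenarios, with 1,500 trials each, gave gains of 0.8 to 4.8 points. The six scenarios do not include the extreme corners of the assumed range.

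**4. Check by formula at two-sided 0.05.** Take q = 20%, p₁ = 80%, p₀ = 42.5%. The conditional odds ratio that yields 70% overall is 2.489, giving treated rates of 90.9% and 64.8%.

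- Adjusted variance: [0.2(0.083 + 0.160) + 0.8(0.228 + 0.244)]/123 = 0.427/123. Power = Φ(0.2/0.0589 − 1.96) = 92.5%.
- Unadjusted variance: 0.46/123. Power = Φ(0.2/0.0612 − 1.96) = 90.5%.

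Over a wider grid (q 10-30%, p₁ 60-90%), adjusted power runs from 90.6% to 95.8%, a gain of 0.1 to 5.3 points.

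**5. Size of a chance imbalance.** One standard deviation of the between-arm difference in q is √(2q(1 − q)/123), or 5.1 points at q = 20%. Multiplied by p₁ − p₀ = 37.5 points, it moves the unadjusted difference by 1.9 points. Over the wider grid the range is 0.4 to 3.3 points, against a 20-point target. The standard error of the unadjusted comparison already allows for this.

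**6. How often the rule admits type.** If P < 0.05 is a test of baseline imbalance, then under valid randomisation it is met in about 5% of trials, however prognostic type is.

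**The case against.** The strongest reply is that the plan already has a safeguard. Imbalance is to be judged by ratios of proportions, and P < 0.05 can be read as significance in the outcome model, not as a baseline test. At an imbalance just short of P < 0.05 (7.5 to 11.5 points between arms), the ratio of shares is about 1.5 to 2.2, which would be noticed. In the six prognostic scenarios, adjustment at that imbalance changes the odds ratio by 9-35% when the imbalance disfavours moxibustion (over 10% in five of six). When it favours moxibustion the change is only 5-7%.

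This reading is possible, so the rule cannot be called a near-absent safeguard on every reading. It does not rescue the rule, however. Whether type enters would depend on the direction of a chance imbalance. The conditional odds ratio also exceeds the marginal one even under perfect balance (2.632 against 2.333 at q = 30%, p₁ = 80%, a 12.8% change), so the 10% criterion does not measure imbalance alone.

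Also correct: randomisation leaves no systematic bias, the gain is small, and its size rests on assumed inputs. Choosing fixed covariates is partly a matter of preference.

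A reader might infer more than the documents support:

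- **That mixed lies explain the 50% control rate.** The Background gives 50% as the control-group rate in the authors' review and attributes it to nothing.
- **That the Background shows the types differ.** Breech at 3-4% and all non-cephalic births in Spain at 3.8% come from different sources and cannot be subtracted. Neither is a version rate by type.
- **That lie is the main source of outcome noise.** Even in scenarios chosen so that type matters, it explains only about 2-15% of the variance.
- **That cephalic at term is a flawed endpoint because it simply reverses the entry criterion.** It is a categorical outcome that matches the research question, and the control arm keeps the comparison fair.

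**Conclusion.** The point holds as one of precision and pre-specification. The fixed covariate list omits the baseline category of the outcome variable, which is recorded but not stratified on, and the only stated route to adjustment is data-driven and ambiguously worded.

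The size is modest: about 1 to 5 points of power in the six prognostic scenarios at two-sided 0.025, and essentially nothing lost if type is not prognostic. That size depends on an assumed share of oblique and transverse lies and assumed version rates by type. The omission itself can be read directly from the text. It does not bias the randomised comparison, and it does not make 492 or the planned power wrong.

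**What to change.** In the Statistical analysis section, add baseline type of presentation (breech against oblique or transverse) to age, parity and weeks of gestation as a fixed covariate of the primary logistic model, whatever imbalance is observed. Report the difference in proportions beside the adjusted odds ratio, because the latter is conditional on type and will not equal the marginal odds ratio. A supporting table of success rates by arm and baseline type would help readers.

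The cost is one more model term and a sentence in the plan. No new data and no extra women are needed, and the sample size stays as it is. The change should be made before outcome data are examined, including at the intermediate analysis.

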### Randomization and treatment allocation

The randomization of the three branches of the study will be carried out on a centralized basis, by a statistician who is otherwise unrelated to the study, using a 1:1:1 scheme in blocks of 12 and stratifying by clinics. There will be the same number of sets of envelopes as there are of participating midwives/clinics (some 40 midwives are expected to take part). Each set will contain 12 opaque envelopes which will be sealed after the introduction of a card with the letter corresponding to the allocation to the group as determined by the software-generated sequence: Group A (true moxibustion), Group B (sham moxibustion) and Group C (control). After the baseline assessment and the signing of informed consent, these sealed, opaque, numbered envelopes will be used in sequence to assign the study subjects to one of the three groups. The collaborating midwife will note on the card the pregnant woman number and that of the clinic. At the end of the study, the chief researcher will check each card against the original randomization list to confirm that all the subjects received the treatment that had been assigned to them. This method ensures that neither the clinics nor the healthcare professionals taking part in the study will be involved in the randomization process and thus will not be able to influence it. A patient may be withdrawn from the study at any time, at her discretion or that of the researcher. The reasons for this will be noted down on the summary page of the Data Collection Record (DCR). The midwives who participate in the study have attended a 10-hour training course on postural recommendations and moxibustion techniques, and in which criteria for data collection were standardised.

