#### Statistical analysis

In the first place, we will perform an analysis following intention-to-treat principles, including all the subjects with valid data, irrespective of whether or not they received the treatment assigned. These results will be compared with those obtained by an on treatment analysis, in order to determine whether violations of the protocol led to bias. The subjects for whom deviations from the protocol are observed – such as not having received the complete treatment, or as having received insufficient follow up, will be excluded from the per treatment analysis. A comparison will be made of respondents and non-respondents to reveal the existence of any selection or classification bias.

Comparability between the interventions and usual care groups will be assessed at baseline to evaluate the differences. The magnitude of the difference in any imbalance produced by the random assignation to the groups will be evaluated using means and proportions ratios (using that of the usual care group as the reference level).

In the bivariate analysis of the magnitude of the association between exposure and effect, diverse tests of statistical significance will be employed to make comparisons between *k *samples (parametric or otherwise, depending on the asymmetric or otherwise distribution of the results variables and on the homogeneity of their variances), taking the usual care group as the reference level and using comparison tests for differences in proportions in the primary outcome measure.

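### The last step of the primary-outcome model adds covariates by baseline imbalance, P < 0.05 and a 10% change in the odds ratio, so the final adjusted estimate is not fixed in advance

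*Protocol article*

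**What the plan says.** The primary outcome is binary: "The rate of cephalic presentation at term will be taken as the primary endpoint variable" (Primary outcome). The Statistical analysis section builds its logistic model, by intention to treat, in three steps.

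1. Treatment group alone: "These will include, firstly, the group variables (experimental vs control), taking the control group (usual care) as the reference level".
2. Three covariates named in advance: "Then, the model will be adjusted for the variables of age, parity and weeks of gestation at randomization (the baseline variables").
3. Further covariates chosen from the data: "Adjustment will also be made for other possible confounders (the variables that are imbalanced in the baseline analysis) using criteria of statistical significance" at P < 0.05, and by a criterion of confounding, a "change of over 10% according to the magnitude estimator", which is the odds ratio.

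The same section says where imbalance comes from and how it is judged: "The magnitude of the difference in any imbalance produced by the random assignation to the groups will be evaluated", by ratios of means and proportions against usual care. It gives no threshold for calling a variable imbalanced. It also plans simple comparisons of proportions for the primary outcome.

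**The concern.** Allocation is randomised, "using a 1:1:1 scheme in blocks of 12 and stratifying by clinics", so a baseline difference between arms is chance, as the plan itself says. Step 3 nevertheless treats such a difference as possible confounding. Its second criterion admits a covariate because that covariate moves the treatment effect, so the content of the last model depends partly on the result it is meant to estimate.

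A 10% shift is also not a clean sign of confounding when the measure is an odds ratio. Adding a strongly prognostic covariate changes the odds ratio even without imbalance, because a conditional odds ratio is a different quantity from a marginal one.

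Two points inside the stated rule stay open: whether both criteria must be met, and which of the three models gives the primary result. At stake is whether the headline odds ratio, and the quantity it estimates, are settled before the data are seen.

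**Working it through.** **Inputs from the protocol.** Rates of 70% and 50% (Background); 492 women, 90% power, 5% significance and 25% dropout (Sample size); 1:1:1 allocation (Randomization and treatment allocation); thresholds of P < 0.05 and 10% (Statistical analysis). Two-sided testing is assumed because sidedness is not stated. The number, strength and independence of candidate covariates are also assumptions, since the protocol gives no prognostic strengths.

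**1. The plan's own figure.** n per arm = [1.960·√(2·0.6·0.4) + 1.282·√(0.7·0.3 + 0.5·0.5)]² / 0.2² = (1.358 + 0.869)² / 0.04 = 124. With 25% dropout, 124/0.75 gives 166 per arm, or 498 in total. Starting from 123 per arm, 123/0.75 × 3 = 492 exactly, with power 89.8%. So 123 evaluable women per arm is used below.

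**2. How often chance alone would offer a covariate.** Suppose P < 0.05 is a baseline test and the k candidates are independent. The chance of at least one significant imbalance is then 1 − 0.95^k: 23% for k = 5, 40% for k = 10 and 54% for k = 15. The Secondary outcomes section lists about 13 baseline variables beyond the three named ones, including "type of presentation, determined by echography (characterized as breech, oblique or transverse presentation"). For k = 13 the chance is 1 − 0.95^13 = 49%, and less if they are correlated.

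**3. What a 10% shift can mean.** The marginal odds ratio is (0.7/0.3)/(0.5/0.5) = 2.33. Take a binary covariate with 50% prevalence in each arm, independent of arm, with outcome odds ratio 5.
- Control arm: ½·expit(a) + ½·expit(a + ln 5) = 0.5 gives a = −0.805.
- Treated arm: ½·expit(a + b) + ½·expit(a + ln 5 + b) = 0.7 gives b = 0.980.
- The conditional odds ratio is e^0.980 = 2.66, a shift of +14% with no confounding.

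The shift is +6.3% for a covariate odds ratio of 3 and +10.3% for 4. For a normal covariate it is +9.2% at an odds ratio of 2 per SD and +15.8% at 2.5. It is zero when there is no treatment effect. So non-collapsibility alone passes 10% only for strong covariates.

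**4. Simulation of the rule.** Comparison of A with C, 123 per arm, three fixed covariates and ten candidates, three of them prognostic (odds ratio 1.8 per SD). P < 0.05 is taken as the baseline test. There were 4,000 null trials and 2,000 with a conditional log odds ratio of 1.0, all tested at a nominal 5%.

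| Model | Covariate added, null | Type I error | Covariate added, effect | Average OR | Power |
|---|---|---|---|---|---|
| Unadjusted | – | 4.85% | – | 2.27 | 86.2% |
| Three fixed covariates | – | 5.1% | – | 2.36 | 88.0% |
| Both criteria required | 13.4% | 4.8% | 9.8% | 2.39 | 88.7% |
| Either criterion enough | 57.8% | 6.0% | 76.6% | 2.67 | 91.7% |

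Average OR is the exponential of the mean log odds ratio. The Monte Carlo standard error of type I error is √(0.05·0.95/4,000) = 0.34 points, so only the last row is clearly above 5%. The 10% criterion alone was met by at least one candidate in 38% of null trials and 64% of trials with an effect. Reporting the smallest P of the unadjusted, three-covariate and both-criteria models gave 6.1%.

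A second simulation (12 candidates, three prognostic with log odds ratio 0.6 per SD, 12,000 null trials) gave 4.7% with both criteria and 5.9% with either.

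**5. The other reading of P < 0.05.** If it means the covariate's significance in the outcome model, with the 10% change also required, 3,000 null trials gave 5.6%. The same run gave 6.2% with the three prognostic covariates always included (standard error √(0.05·0.95/3,000) = 0.40 points). That run shows no excess attributable to selection.

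**6. Meaning of the move from 2.36 to 2.67.** Given all covariates, the simulated odds ratio is e^1.0 = 2.72. The selected model moves towards that more conditional quantity. What the last model estimates thus depends on which covariates happened to enter.

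**The case against.** The strongest reply is that the selection is only the third step. An unadjusted model and a model with three named covariates come first, and a simple comparison of proportions is planned as well. A reader might infer that the whole primary analysis is chosen after the effect is seen; the text does not support that. A statistical analysis plan, not shown here, may also name the primary model. This stands, and it confines the point to the final adjusted estimate. It does not remove the point, because the selection rule is written out in the protocol rather than left open.

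Second, imbalance is to be judged by ratios, so P < 0.05 may refer to the covariate in the outcome model. On that reading it cannot be said that the rule ignores prognosis. The choice would still be made from the data.

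Third, a perfectly balanced covariate should not pass a screen for imbalance, so the +14% example is not a case that the rule would admit. It shows only that part of an imbalanced covariate's shift can be non-collapsibility, and that this part is large only for strong covariates.

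Fourth, one might infer that nominal P values fail or that power is lost. The simulations do not show this. With both criteria required, as the word *and* in the text suggests, type I error stays near 5%. A power contrast of 88.7% against 93.4% can be produced in the second simulation, but only by a comparator that already knows which candidates are prognostic. Against the three-covariate model in the table there is no loss. Nor does adjustment narrow the log odds ratio: its standard deviation rose from 0.275 unadjusted to 0.285 with the three fixed covariates.

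**Conclusion.** The point holds in limited form. The third modelling step makes the final adjusted odds ratio for the primary outcome data-driven and partly dependent on the observed treatment effect. It does so to correct an imbalance that the plan itself attributes to chance, using a criterion that cannot fully separate imbalance from non-collapsibility.

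The error-rate cost is small: about 5% if both criteria are required and about 6% if either is enough. The shift in the average odds ratio is slight on the first reading (2.36 to 2.39) and material on the second (2.36 to 2.67). These sizes rest on assumed covariate strengths, independent candidates, one pairwise contrast and a nominal 5% test without the interim penalty.

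The main harm is that the estimate and estimand are not fixed in advance, made worse by the open questions of how the criteria combine and which model is primary. The protocol does not show that type of presentation or placental location predicts version, so their absence from the named covariates is not a fault that can be established here.

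**What to change.** Name one primary analysis: the logistic model with treatment arm, age, parity and weeks of gestation at randomisation, all already listed. Add another collected baseline variable only if it is chosen beforehand on prognostic grounds. Delete the P < 0.05 and 10%-change rules from the primary model. Keep the unadjusted comparison, and any adjustment for observed imbalance, as labelled sensitivity analyses.

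The cost is wording only: the sample size of 492 is unchanged and nothing new need be collected. In the simulation the fixed three-covariate model had a type I error of 5.1%. The one downside is that a large chance imbalance in an unlisted variable would be addressed only in the sensitivity analysis.
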